# A novel behavioural INTErvention to REduce Sitting Time in older adults undergoing orthopaedic surgery (INTEREST): protocol for a randomised controlled feasibility study

**DOI:** 10.1186/s40814-019-0437-2

**Published:** 2019-04-06

**Keywords:** Osteoarthritis, Sitting, Elderly, Older adults, Sedentary behaviour, Arthroplasty, Prehabilitation, Intervention, Feasibility study, Behaviour modification

## Abstract

**Background:**

Osteoarthritis is a highly prevalent condition in older adults, that causes many sufferers to require a hip or knee replacement in order to improve their quality of life and reduce pain. Individuals waiting for hip or knee replacements are often highly sedentary; thus, it is pertinent to assess whether reducing their sedentariness prior to surgery may aid in improving post-operative outcomes.

**Methods/design:**

The study will be a randomised controlled feasibility trial design, with 2:1 randomisation into an intervention and usual care group respectively. A target of 45 patients aged 60 years or older waiting for elective hip and knee replacements will be recruited from Russells Hall Hospital, Dudley, UK, approximately 8–10 weeks before surgery. The intervention, informed by Self-Determination Theory (SDT), will be composed of multiple behaviour change techniques, namely, motivational interviewing, feedback on current objectively measured sedentary behaviour and activity, goal-setting, environmental modification, self-monitoring, and social support. Assessments will occur at baseline, 1 week pre-surgery, and 6 weeks post-surgery. The primary outcome will be the feasibility of intervention delivery and of the trial procedures, assessed quantitatively based on rates of recruitment, retention, measures-completion, and intervention fidelity assessment, and with mixed-methods assessment of acceptability, practicality, adaption, satisfaction, and safety. Exploratory outcomes will include physical function, cardiometabolic biomarkers, measurement of SDT constructs, and both objective and subjective measurement of physical activity and sedentariness. The study will last up to 18 weeks per participant. No formal between-group comparisons are planned, but the variance in within-group changes and differences between groups in outcome measures will be explored and reported with 95% confidence intervals.

**Discussion:**

This is the first study assessing the feasibility of an intervention to reduce sedentary behaviour in older adults with mobility limitations, and the first to assess whether such a reduction could work in a prehabilitative context prior to surgery. The results of this study will help inform the design of a definitive randomised controlled trial.

**Trial registration:**

This trial is registered on Clinicaltrials.gov. Registration number: NCT03740412. Date of registration: 13/11/2018.

**Electronic supplementary material:**

The online version of this article (10.1186/s40814-019-0437-2) contains supplementary material, which is available to authorized users.

## Background

Sedentary behaviour, defined as “any waking behaviour characterized by an energy expenditure of ≤ 1.5 metabolic equivalent of tasks (METs) while in a sitting or reclining posture”, is associated with negative health outcomes [1]. In older adults, evidence suggests there is an association between sedentary behaviour and physical function, as well as cardiovascular disease, type II diabetes risk, and overall mortality [2, 3]. One study found that each additional 1-h period of sitting time per day is associated with a clinically significant reduction in physical function of 0.55 points of the Short Physical Performance Battery (SPPB) score [4, 5]. This is of particular concern, as studies using an objective measurement of sedentary behaviour have found that older adults (≥ 60 years old) spend an average of 8.5 h per day sitting [6].

Given the high degree of sedentariness in older adults, in combination with the mounting evidence of the associated health risks, several interventions aiming to reduce sitting time in older adults have been reported [11]. These include interventions to displace sedentary time to light physical activity such as walking, or simply other standing activities [7–12]. However, existing interventions have suffered several shortfalls. They are often feasibility trials with small sample sizes, and can lack objective measurement of sedentary behaviour using an inclinometer or accelerometer. Often, they have not assessed changes in blood biomarkers or physical function post-intervention, nor have they included follow-ups to assess the duration of behaviour change conferred [11]. Very few such trials have adequately reported the theoretical basis or provided a logic model underpinning their behaviour change intervention. Additionally, they have all included healthy older adult populations without significant comorbidity [11].

Older adults often have morbidities which can lead to even greater sitting time due to pain or other factors [13]. One such condition is osteoarthritis, which is extremely prevalent in older adults. In the UK, 18.2% of adults ≥ 45 years have osteoarthritis of the knee, and 10.9% have osteoarthritis of the hip [14]. Osteoarthritis causes chronic pain and further predisposes patients to be more sedentary. According to an analysis of objective sedentary behaviour data, individuals with mobility limitations have more sedentary time, less active time, and longer sedentary bouts compared with healthy controls [15]. Likewise, a recent review has identified that despite a reduction in pain after total hip or knee replacements, older adults do not return to being as active as their healthy counterparts [16].

Yet, no intervention to date has attempted to reduce the sedentary time in older adults with mobility limitations, despite the benefits it may bring to this at-risk population, and reducing sedentary behaviour in a prehabilitative context has not been explored. However, other studies to increase physical activity prior to arthroplasty have been found to be effective at improving physical function. A prior intervention utilising resistance, flexibility, and step training prior to knee arthroplasty in adults (*n* = 26) with a mean age of 64.1 has been found to be effective at reducing pain and improving sit-to-stand function [17]. Similarly, a study investigating the efficacy of a personalised physiotherapy programme in severely disabled adults (*n* = 28) with a mean age of 66.5 prior to knee or hip arthroplasty found significant improvement in timed up-and-go, self-paced walk, and timed stair tests after prehabilitation [18]. In terms of sedentary behaviour interventions, a previous study in older adults (*n* = 38) 60 years and over has found it possible to improve SPPB score by 0.5 points, a clinically meaningful increase, after a 12-week sedentary behaviour reduction intervention [19]. These data suggest that it may be possible to improve physical function simply by reducing sedentary behaviour. This may have potential as a method of prehabilitation.

### Aims

This study will assess the feasibility of delivering a novel intervention to reduce sedentary behaviour in a population of adults ≥ 60 years awaiting hip and knee arthroplasties in comparison with usual care. It will also assess the feasibility and acceptability of conducting the procedures required to conduct a full-scale RCT, by incorporating measurement of physical function, blood markers, objective measurement of sedentary behaviour, and physical activity, with both pre- and post-operative measurements.

The *primary* aim is to assess the study feasibility quantitatively using statistics related to the delivery of the study (uptake rate, recruitment rate, intervention adherence, delayed surgery, early surgery, cancelled surgery, retention rates, duration of intervention, session attendance); the *secondary* aim is to assess the feasibility outcomes of acceptability, practicality, satisfaction, and safety of the study in both arms using mixed methods; and the *exploratory* aim is to assess which of the efficacy measures (i.e. SPPB, cardiometabolic biomarkers, objectively measured sedentary time) are most promising for the design of a future clinical trial.

## Methods

This article has been written following both SPIRIT and TiDIER guidelines [20, 21].

### Study design

This is a single-site, parallel group, pragmatic randomised controlled feasibility trial design using 2:1 allocation into an intervention and usual care group, respectively.

### Study setting

This single-site study will be conducted at Russells Hall Hospital, Dudley, UK. Study procedures and intervention/assessment visits will take place either at participants’ own homes, at the hospital, or at the University of Birmingham, Birmingham, UK. This range of options is intended to decrease the burden to the participants.

### Patient identification

Patient lists obtained from orthopaedic clinicians by research nurses at Russells Hall Hospital will be screened for individuals fulfilling the study criteria. Patients will not be taking part in other interventions during participation in this study.

### Inclusion and exclusion criteria

Patients will be eligible if they are:A man or woman aged ≥ 60 years.Listed for elective hip or knee surgery.Capable of providing informed consent as determined by their primary care team from medical records.Regular access to a phone at pre-specified times.Able to speak English.

They will be excluded if any of the following apply:Neuromuscular impairments that preclude participating in physical activity, visual, hearing, or moderate/severe cognitive impairments as indicated by medical notes prior to recruitment.Significant comorbid disease that would pose a safety threat, affect blood measures significantly, or impair the ability to participate in physical activity.Unwillingness or inability to comply with the intervention.

### Recruitment process

The research nurses working at Russells Hall Hospital will screen patient lists to identify patients scheduled for hip or knee replacements and who meet inclusion and exclusion criteria. Research nurses will send participant information sheets (PIS) by post to eligible patients, and the patients will be asked to either return an enclosed contact agreement form or contact the research team by phone or email directly to indicate their interest in taking part (Fig. 1). Research nurses will also phone the participant 1 week after sending the PIS to ask whether they are interested in taking part. Wherever possible, patients will be enrolled in the study 8–10 weeks prior to their estimated surgery date.

**Fig. 1 Fig1:**
[figure not shown]
Study schema

### Sample size

A power calculation informed us that a sample size of 44 is sufficient to allow estimation of the retention rate of a future clinical trial with 95% confidence intervals of ± 11%, given an expected retention rate of 80%. For this reason, this study aims to recruit 45 patients, with 30 randomised to the intervention group and 15 to the usual care group. This sample size is also consistent with advice from clinicians about expected uptake rate and sample sizes used in prior feasibility studies to reduce sedentariness in older adults [11] This sample will be recruited over a 12-month period.

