### Study assessments

#### Primary outcome assessment

##### Feasibility (study statistics)

Feasibility will be assessed primarily using the following study statistics:Study uptake rate—percentage of participants whom receive a PIS who subsequently enrol in the study (%).Recruitment rates—average number of participants recruited per month.Intervention adherence—average self-reported goal adherence (scale 1–5) per week (recorded in sedentary behaviour booklet).Percentage of participants whose surgery occurs eight or more weeks after visit 3 (%).Percentage of participants whose surgery is scheduled four or fewer weeks after visit 3 (%).Percentage of participants with indefinitely delayed or cancelled surgery—proportion of participants who will not have surgery within the lifetime of the study (%).Retention rates—percentage of participants who remain in the study (i.e. provide measures) and do not drop-out at each follow-up timepoint (%).Average duration of intervention—average number of weeks of participation in the intervention prior to surgery.Session attendance—number of intervention sessions attended and the associated total contact time.

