### Progression to a definitive trial

Progression to a definitive trial will be considered if the following metrics are met:A minimum of 75% of patients have their surgeries within 10 days of the 4–8-week intervention window between visit 3 and visit 4.Rate of uptake meets or exceeds 10%.Participant retention rate exceeds 75% between baseline and pre-surgery visits.Study satisfaction must be ≥ 4/5, and risk of harm should be < 2/5, as assessed by the feasibility questionnaire given to participants.The frequency of adverse events does not call into question the safety of the trial as determined by the medical expert on the study ([name]).

The rationale for these criteria is as follows:Participants need to have their surgery within a specific timeframe to keep the intervention length somewhat equivalent. This may be alleviated if a definitive trial was multisite.Based on advice from clinicians, approximately 300 patients are likely to be eligible to be sent a PIS over the 12-month recruiting period. An uptake rate of 10% would be below the target of 45 but would inform us that a multisite strategy would be necessary for the definitive trial.A high number of drop-outs would inform us that the intervention is not acceptable in its current form. The post-surgery visit (visit 5) is not used as a criterion here, as whether patient surgeries are cancelled or delayed is unlikely to be related to study procedures.The study should be perceived as safe and acceptable by participants.Safety should be of primary concern, as increased walking and standing could potentially increase the risk of falls in this population.

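### The stated ±11% precision for an 80% retention rate does not follow from 44 patients; the inputs give about ±12 points

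*Protocol article*

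**What the plan says.** The Sample size section gives one calculation. Its claim reads: "sample size of 44 is sufficient to allow estimation of the retention rate of a future clinical trial with 95% confidence intervals". It puts the half-width at ±11%; the condition attached is "given an expected retention rate of 80" per cent. It then concludes that "this study aims to recruit 45 patients, with 30 randomised to the intervention group and 15 to the usual care group". No formula, interval method or correction is named. The section adds two non-statistical supports for the size: clinicians' advice on uptake, and the sizes of earlier feasibility studies.

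Under Feasibility (study statistics), retention is the "percentage of participants who remain in the study (i.e. provide measures) and do not drop-out at each follow-up timepoint". Under Progression to a definitive trial, one criterion is "Participant retention rate exceeds 75% between baseline and pre-surgery visits". The same section reports that "approximately 300 patients are likely to be eligible to be sent a PIS over the 12-month recruiting period", and uses that number to explain the 10% uptake criterion.

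**The concern.** The precision sentence supplies everything needed to check it: sample size, confidence level, expected proportion and half-width. The four do not fit together. The half-width that follows from the other three is wider than stated, and the sample size that follows from the stated half-width is larger than 44.

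This is the only calculation behind the sample size, and retention is both a primary feasibility statistic and a progression criterion. Someone planning the definitive trial may take ±11% as a property of the design. What is at stake is the accuracy of that statement, not the conduct of the study.

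**Working it through.** **Inputs.** From Sample size: n = 44, expected retention p = 0.80, 95% confidence (z = 1.96), stated half-width d = 0.11, target 45 split 30 and 15. From Feasibility (study statistics): retention is a percentage of participants, so the denominator is everyone enrolled. No inflation for drop-out enters the calculation.

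**Attempt to reproduce the stated figure.** Wald half-width = z × √(p(1 − p)/n).

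- n = 44: 1.96 × √(0.16/44) = 0.118, or 11.8 points.
- n = 45: 1.96 × √(0.16/45) = 0.117, or 11.7 points (68.3% to 91.7%).

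Solving for n: n = z² × p(1 − p)/d² = 0.16 × (1.96/0.11)² = 50.8, so 51 patients, 7 more than stated.

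**Other interval methods at n = 44.**

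| Method | Half-width (points) |
|---|---|
| Wilson, p = 0.80 | 11.6 |
| Agresti–Coull, p = 0.80 | 11.8 |
| Wald with continuity correction, p = 0.80 | 13.0 |
| Exact (Clopper–Pearson), 36/44 or 35/44 | 12.3 or 12.8 |

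All of these round to 12 or more. By Wilson, ±11 points needs about 49 to 50 patients. Changing the confidence level does not help: a 90% Wald interval at n = 44 is ±9.9 points, and ±11 points at 90% would need 36 patients.

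**At the recruitment target, 36 of 45 retained (exactly 80%).** Wilson: 66.2% to 89.1%, half-width 11.5. Exact: 65.4% to 90.4%, half-width 12.5.

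**One route to 44.** Apply a finite-population correction with N = 300: n = 50.8/(1 + (50.8 − 1)/300) = 50.8/1.166 = 43.6, rounded up to 44. The half-width at n = 44 is then 11.82 × √((300 − 44)/(300 − 1)) = 10.9 points. Any N from about 275 to 322 also gives 44.

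**Intervention arm alone, n = 30.** 1.96 × √(0.16/30) = 0.143, or 14.3 points.

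**The case against.** The strongest reply is that the gap is a matter of rounding. The study recruits 45, not 44, and at 36/45 the Wilson and Jeffreys half-widths are each about 11.5 (11.46 and 11.47), which round down to 11. At 36/44, Wald gives 11.4 and Wilson 11.2. Truncating 11.8 would also print as 11. This stands in part: it would be wrong to say that no uncorrected method can ever print ±11%. But the sentence says 44 and 80%; 36/44 is 81.8%; and truncation is itself an error. Nor is the Wilson interval at 45 symmetric about 80%: it reaches 13.8 points below and 9.1 above, so a plus-or-minus figure describes it poorly.

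A second reply is that nothing depends on the figure. The progression rule compares observed retention with 75% and uses no interval, and the Data analysis section already plans confidence intervals among the descriptive statistics for feasibility. This stands, and it limits the point to a correction of wording.

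A reader might infer from the match at N = 300 that the sponsor applied a finite-population correction. The article does not support that as a finding. It mentions no correction, it uses the figure of 300 only to explain the uptake criterion, and a range of other values of N gives the same answer. If a correction was used, it would not suit the stated target: patients in a future trial, for which the article contemplates several sites, are not a fixed list of about 300 from which 44 are drawn.

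**Conclusion.** The precision statement is wrong as written. With its own inputs the 95% half-width is 11.8 points (Wald) or 11.6 (Wilson), not 11, and ±11 points needs 51 patients by the standard formula. The error is 0.6 to 0.8 of a percentage point by these two methods. This rests on simple binomial sampling, retention counted over all participants, and the stated 80%.

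Two stronger readings should be resisted. The gap of 7 patients does not show that the study is too small: the article sets no requirement that depends on exactly ±11%, and it also bases the size on expected uptake and earlier studies. Nor does the error undermine the 75% retention criterion, which is a point-estimate rule. The ±14.3 points for the 30 intervention patients is useful context, but it is not part of the error, because the article states its precision for the study as a whole. The origin of the figure 44 remains unknown.

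**What to change.** Keep the target of 45 and replace the precision sentence with one that names its method, for example: *With 45 patients and an expected retention of 80%, the 95% Wald confidence interval is about ±12 percentage points (68% to 92%); the Wilson interval is 66% to 89%.* The two methods should be kept apart in this way, because a ±12 beside Wilson limits would not agree with them.

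Optionally add that for the 30 intervention-arm patients alone the Wald half-width is about ±14 points. If ±11 points is really required, the standard formula asks for 51 patients, but nothing in the article calls for that. If a finite-population correction was in fact used, say so and remove it.

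The cost is one sentence and a slightly less favourable stated precision, with no change to recruitment, allocation, analysis or progression criteria.

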### Informed consent

The patient will provide written informed consent at the initial study visit.

### Randomisation and group allocation

Due to the nature of the intervention, it is not possible to blind participants or the data-collecting researcher to group allocation. Randomisation will be conducted using 2:1 permuted block randomisation by a third-party researcher, not affiliated to the project, who will retain allocations in confidence. This 2:1 allocation ratio was chosen to increase the number of people in the intervention group to allow for greater assessment of the feasibility of the intervention (Table 1). The primary researcher will be blinded to the allocation until the date of the visit in which the intervention must be delivered for each participant.

**Table 1 Tab1:** Template for Intervention Description and Replication (TIDieR) checklist table [21]

Brief name	Pre-surgical sedentary behaviour reduction in orthopaedic patients
Why	Reducing sedentary behaviour prior to surgery has the potential to improve physical function and cardiometabolic health, leading to better post-surgical recovery.
What (materials)	As part of the intervention, a custom-made booklet will be used to aid in delivery of the education, goal setting, and environmental modification components, with space to record adherence to planned actions and environmental modifications.
What (procedures)	The intervention itself consists of a few key procedures: 1. Motivational interviewing to reduce ambivalence towards sedentary behaviour. 2. Education about sedentary behaviour and its negative health consequences. 3. Goal-setting and environmental modification. 4. Self-monitoring using a pedometer and recording of goal adherence. 5. Biweekly phone calls to maintain participant motivation and address issues.
Who provided	The intervention will be delivered solely by a trained researcher (JA), who has had training in motivational interviewing and who designed the intervention and materials. In this manner the intervention delivery will be very consistent.
How	Intervention content will be provided in a face-to-face and one-to-one context.
Where	The intervention and assessment sessions will occur mostly in participants’ own homes, but some sessions can occur at Russells Hall Hospital or at the University of Birmingham.
When and how much	The intervention can be delivered in 120 min in a single session followed by three 10-min biweekly phone calls. However, the study also includes 3 assessment points at baseline, 1 week pre-surgery, and 6 weeks post-surgery. Participants are expected to join the study 8–10 weeks before their surgery, and total study duration may last up to 18 weeks per participant.
Tailoring	As the goals and environmental modifications are the active behaviour change component of the intervention, each participant will have a wholly bespoke experience tailored to their individual capacity for physical function and their lifestyle.
Modifications	Goals and environmental modifications may be altered at any point by the participant if they are finding it hard to achieve, e.g. they could lower their step count target, or alter the frequency of another goal’s occurrence. The researcher will stay informed of these changes using the phone calls.
How well planned (fidelity)	A subset of the motivational interviews will be recorded and assessed for quality against a checklist of motivational interviewing techniques and content. An additional subset of these interviews will be recorded using field notes. A subset of phone calls will be checked for content delivery by the researcher against a purpose-built checklist. Action plans will be checked by an independent reviewer for adequacy, adherence to SMART principles, and appropriateness to the participant.

